## Introduction

Hypertension is one of the major risk factors for fatal complications of cardiovascular disease [1-4] and represents a significant public health concern worldwide. Annually, hypertension is responsible for approximately 10.4 million deaths [5]. Therefore, the primary goals of hypertension management are to regulate blood pressure and prevent damage to target organs [6-8]. In 2015, the global prevalence of adults with elevated blood pressure reached 1.13 billion [9], with projections indicating an increase to 1.56 billion by 2025 [10], thereby posing a considerable global health and socioeconomic challenge [11]. The pathophysiology of essential hypertension is intricate, and its etiology is not yet fully elucidated [12]. Although antihypertensive medications have traditionally been the cornerstone of hypertension management, many patients experience inadequate blood pressure control [13]. Approximately 50% of patients discontinue antihypertensive medications within the first year [14], and adherence rates are generally low [15]. Approximately 9% of patients with hypertension discontinue their medication due to adverse side effects [16]. Furthermore, a significant proportion of patients with hypertension continue to experience severe symptoms associated with hypertension, such as headache, dizziness, and insomnia [17-19]. Consequently, the search for effective and low-harm alternative or complementary therapies has become a critical goal in the management of hypertension [20].

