**Inclusion criteria**
18 years old ≤ age ≤75 years old, both male and female individuals.Those who meet the diagnostic criteria for primary hypertension in the International Society for Hypertension’s 2020 Practice Guidelines, with a hypertension classification of grade 1 and a risk stratification of low to moderate risk; and those who receive acupuncture treatment while their original treatment is not changed;Those who had not taken medication in the past, with an office systolic blood pressure of 140-159 mm Hg and/or a diastolic blood pressure of 90-99 mm Hg; and those who had not changed medication for at least 1 month in the past, with an office systolic blood pressure of 120-159 mm Hg and/or a diastolic blood pressure of 80-99 mm Hg. The types of antihypertensive drugs used are calcium channel blocker+angiotensin converting enzyme inhibitor/angiotensin II receptor antagonist, but no more than two types;Correct understanding of the significance of this clinical study, good compliance with the observations and evaluations of the investigators, and voluntary signing of an informed consent form by the participant himself/herself.

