#### Secondary Outcomes

Some of the symptoms associated with essential hypertension, such as vertigo, headache, and insomnia, will be assessed using scales such as the Dizziness Handicap Inventory (DHI), Headache Impact Test-6 (HIT-6), and the Pittsburgh Sleep Quality Index (PSQI). The DHI is a classic tool for assessing vestibular or dizziness-related dysfunction and contains 25 entries covering functional, affective, and somatic dimensions [40]. In hypertensive patients, dizziness is a common symptom that may be associated with blood pressure fluctuations or medication side effects. The HIT-6 is a 6-item questionnaire that assesses the impact of headache on daily functioning in patients with hypertension associated with headache (eg, migraines or medication-induced headache) [41]. The PSQI is a 19-item tool that assesses sleep disorders, which are often comorbid in patients with hypertension (eg, insomnia and sleep apnea) [42,43].

The above assessments will be performed at baseline, at week 6 of starting treatment, and at weeks 1, 2, and 4 after the end of treatment. In addition, other safety indicators will be assessed, including general physical examination, liver and renal function and electrocardiogram at baseline. These tests will be performed at baseline and at week 6 of treatment.

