#### Sample Size and Statistical Analysis

The sample size of this study was estimated using the 2-sample *t* test in PASS (Power Analysis and Sample Size Software; NCSS LLC) 11 efficacy. According to existing literature [44], the mean improvement in systolic blood pressure within 24 hours for patients with essential hypertension treated with acupuncture was 8.9 mm Hg, while the mean improvement for those treated with sham acupuncture was 5.4 mm Hg, resulting in a clinical effect difference of 3.5 mm Hg. The SD for each group was 9.9 mm Hg. The sample size calculation assumed a 2-tailed significance level (α) of 0.05 and a statistical power (1-β) of 80%, the total sample size required for acupuncture treatment of mild-to-moderate essential hypertension was calculated to be 102 cases. Accounting for a 10% dropout rate, a total of 228 hypertensive participants needed to be recruited, with 114 participants in each group.

Statistical analyses we will leave to a statistician who is unaware of the groups. Data will be analyzed using the SAS 9.3 and SPSS 29.0 (IBM Corp) packages, and a 2-sided *P*<.05 will be considered statistically significant. We will use the intention-to-treat analysis set for outcome analysis and also validate it using per-protocol analysis to determine if the two results are consistent and inconsistency will require further analysis and discussion. For patients who withdrew from the study midway through the study, baseline data and follow-up data that had been collected before withdrawal were included in the intention-to-treat analysis. Missing values will be interpolated by the last observation carried forward method.

Baseline data on participants’ demographic information and general state characteristics such as age, gender, and disease duration will be represented by descriptive statistics for both groups. We will measure in-office immediate blood pressure values at different time points of the needle prick and 24-hour ambulatory blood pressure values at baseline, week 6 of treatment and week 4 after the end of treatment, and comparisons between groups will be assessed using repeated measures ANOVA.

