For continuous variables, expressed as mean (SD), grouped *t* tests will be used if they conform to normal distribution and vice versa, that is, they will be assessed by Wilcoxon rank-sum test; categorical variables will be compared using chi-square test or Fisher exact test (Fisher), and the results of the data will be documented in the form of percentage.

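### DHI and HIT-6 are scored in all randomised patients although entry requires neither dizziness nor headache, and the planned two-group test makes no stated use of the baseline score

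*Protocol article*

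**What the plan says.** The inclusion criteria in Textbox 1 of the protocol article cover age, diagnosis, office blood pressure, medication and consent. Patients are admitted "with a hypertension classification of grade 1 and a risk stratification of low to moderate risk". Neither list of criteria asks for dizziness or headache or sets a minimum scale score, and neither excludes patients who have these symptoms.

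Under Secondary Outcomes, DHI is presented as a measure of dizziness-related dysfunction, and HIT-6 as a tool that "assesses the impact of headache on daily functioning in patients with hypertension associated with headache". The scales are taken at baseline, at week 6 and at three times after treatment. Table 3 marks them as compulsory and does not limit them to patients with the symptom. On how common the symptoms are, the Introduction says only that "a significant proportion of patients with hypertension continue to experience severe symptoms associated with hypertension, such as headache, dizziness, and insomnia".

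The section Sample Size and Statistical Analysis uses the intention-to-treat set for outcomes, with a per-protocol check. Repeated measures ANOVA is named for blood pressure only. The scales therefore fall under the general rule for continuous variables: "grouped *t* tests will be used if they conform to normal distribution and vice versa, that is, they will be assessed by Wilcoxon rank-sum test". The rule does not say whether follow-up scores or changes are compared, and it mentions no adjustment for baseline.

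**The concern.** The article describes HIT-6 and DHI in terms of patients who have headache or dizziness, but it enrols patients with grade 1 hypertension whether or not they have either. Those without the symptom can sit at the bottom of the scale at baseline, with no room to improve. Two things follow.

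- The all-patient mean difference shrinks in proportion to the share of patients with the symptom.
- A cluster of patients at the floor makes normality doubtful. The stated rule would then lead to a rank-sum test with many ties. If that test is applied to follow-up scores, the ranking mostly reflects who had the symptom at entry and not what treatment did.

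The Discussion relies on DHI, HIT-6 and PSQI to show benefit beyond blood pressure. With a weak test, a null result could not distinguish no symptom benefit from few patients with symptoms to relieve.

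**Working it through.** **Number of patients.** No power is stated for the symptom scales. I take 102 evaluable per group, because 102/0.9 = 113.3, rounded up to 114 per group, gives the planned 228. The article says that the size "was calculated to be 102 cases" and calls it the total. That figure does not reproduce from its own inputs ("resulting in a clinical effect difference of 3.5 mm Hg"; "The SD for each group was 9.9 mm Hg"; two-sided 0.05; 80% power): 2 × (1.960 + 0.842)² × 9.9²/3.5² = 125.6, or 126 per group. That is a separate matter; here 102 only sets the scale.

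**Dilution.** Let p be the share with the symptom at baseline. If the others stay at the floor, then

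all-patient mean difference = p × difference in symptomatic patients.

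In the first model below, an assumed 0.5 SD shift becomes about 0.45 SD in symptomatic patients, because scores are cut off at the floor. At p = 50% the all-patient difference is 0.50 × 0.45 = 0.225 SD. At p = 30% it is 0.30 × 0.45 = 0.135 SD.

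**First simulation model (all inputs assumed).** Symptomatic patients start on average 1.5 SD above the floor. The baseline to week-6 correlation is 0.6, the effect is 0.5 SD, and scores are cut off at the floor. Patients without the symptom stay at the floor. Power of the rank-sum test, two-sided 0.05:

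| Share symptomatic | Week-6 score, all | Week-6 score, symptomatic only | Change, all | Change, symptomatic only |
|---|---|---|---|---|
| 30% | 11% | 46% | 43% | 50% |
| 50% | 24–26% | 70% | 66% | 73% |
| 70% | 51% | 84% | 83% | 86% |

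At 50% symptomatic, ANCOVA on the week-6 score with baseline as covariate gives about 85% in all patients and 88% in symptomatic patients. Repeat runs move these figures by up to about two points.

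**Separating the two steps at 50%.** Using baseline by ranking change in all patients adds 66 − 24 = 42 points. Then restricting to symptomatic patients adds 73 − 66 = 7 points, or 88 − 85 = 3 points with ANCOVA. In this model, most of the recoverable loss comes from ignoring baseline.

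**Second model: ranked changes, with improvement on sham.** Here symptomatic sham patients also improve by 0.5 SD of change, and the others are tied at zero. With a 0.5 SD effect, rank-sum power on change in all patients falls from 94% when all are symptomatic to 49% at p = 50%; symptomatic patients alone give 69%. With 0.4 SD the figures are 79%, 34% and 49%.

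Restriction matters more here because improvement common to both groups separates symptomatic patients from the rest. For the t test at p = 50% and 0.5 SD, the within-group variance of change is p + p(1 − p)m², where m is the mean change in symptomatic patients:

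- acupuncture (m = 1.0): 0.5 + 0.25 × 1.00 = 0.75
- sham (m = 0.5): 0.5 + 0.25 × 0.25 = 0.5625
- all patients: z = 0.25/√((0.75 + 0.5625)/102) = 2.20, power about 60% (simulated 61%)
- symptomatic only: z = 0.5/√(2/51) = 2.52, power about 71%

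The extra variance follows baseline symptom status, so a baseline covariate can take up part of it.

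**Third model: a 0–100 score with a true reduction of 6 points.** At p = 100% and p = 50%, rank-sum power in all patients is 74% and 32% on change, and 42% and 11% on the week-6 score.

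**The case against.** The strongest reply is that nothing here is an error. The intention-to-treat contrast estimates the average effect in the patients enrolled and is unbiased. The scales are secondary outcomes with no stated power. Whether scores or changes are analysed, and any symptomatic subset, may well be settled in an analysis plan that is not shown. Every magnitude is assumed, and a model that holds asymptomatic patients exactly at the floor is an extreme case. All of this stands, and it limits the point to a matter of efficiency.

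Four stronger readings are tempting and not supported.

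- A reader might set 26% against 70% at half symptomatic and blame a 44-point loss on enrolling patients without symptoms. Both figures assume that raw week-6 scores are ranked, which the article does not say. With ranked changes the same model gives 66% against 73%.
- A reader might conclude that the symptomatic subset should be the principal analysis. That changes the question, leaves out patients whose symptoms emerge during treatment, and in the first model adds little once baseline is used.
- A reader might extend the floor argument to PSQI. The article describes it as a tool for sleep disorders and gives no ground for placing patients without insomnia at its minimum.
- A reader might take the criteria to demand patients free of symptoms. They are silent on symptoms.

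What the reply does not remove is that the article itself names the analysis set and the tests, and neither named test is said to use a baseline score that is collected in everyone.

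**Conclusion.** The concern holds as a correctable loss of efficiency for DHI and HIT-6, not as bias. Entry does not ensure that patients have the symptom, all are scored, and the stated test makes no declared use of baseline.

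At an assumed 50% symptomatic and 0.5 SD effect, power in all randomised patients is about 24% for ranked week-6 scores, 66% for ranked changes and 85% for ANCOVA. The direction holds in every model tried. The size depends on the symptom share, the effect, the correlation and the improvement on sham, none of which the documents give. Failure of normality, and hence the use of the rank test, is likely if many patients are at the floor, but it is not established.

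**What to change.** In Sample Size and Statistical Analysis, next to the rule for continuous variables:

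- State that each symptom scale is compared between groups in all randomised patients using the baseline score: ANCOVA on the follow-up score with baseline as covariate, or a rank test on change from baseline if a rank test is needed. Make this the main analysis.
- Pre-specify a supportive analysis in patients who have the symptom at baseline, with the threshold for each scale fixed before unblinding. The subset is defined by a baseline score, so it remains a randomised comparison.
- Report the number symptomatic at baseline in each group for each scale.

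The cost is wording and a little more analysis; Table 3 already schedules the baseline scales. The subset has fewer patients and wider intervals, and its result applies only to patients with the symptom. The article reports 27 participants recruited and no analysis done, so on that status the change can still be made before unblinding.

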#### Patient Safety

During acupuncture treatment, participants may experience adverse events such as bleeding, subcutaneous hematomas, persistent feeling of getting gas, increased pain, infection, needle fainting, stress elevation of blood pressure, and allergic reactions to alcohol. As investigators, we will carefully observe changes in the participant’s vital signs and record them in the CRF at all times.

#### Data Management and Quality Control

A thorough assessment will be performed during the screening and preparation phase of the trial and periodically throughout the trial. The screening phase will last for 1 week and will include assessment of basic information such as gender, age, temperature, heart rate, respiration, BMI, etc, as well as detailed information about the participant's chief complaint, current medical history, past history, family history, routine checkups, blood pressure, and medication use. The timing and process of data collection are detailed in Table 3.

Before the formal commencement of the study, all researchers will undergo a uniform and rigorous training to ensure that they are familiar with and equipped with the diagnostic and therapeutic measures and basic assessment skills to improve the consistency of internal observations. According to the study protocol, we will collect complete and authentic raw data from the participants and keep detailed records. Any data that deviate significantly from the clinically acceptable range must be examined and interpreted. The completed and validated CRF will be given to the relevant personnel for data entry, management and statistics, and the data on the CRF will not be modified. Professionals will be assigned to provide regular supervision and quality control throughout the study.

**Table 3 table3:** Clinical research flowchart.

Phase project	Baseline period	On-treatment			Follow-up period		
	Week 0	Week 1	Week 6	Week 7		Week 8	Week 10
Signed informed consent	✓^a^						
Filling in demographic information	✓						
Previous diseases and medication	✓						
Prestudy medication and other treatments	✓						
General physical examination items	✓						
Physical examination	✓						
Acceptance and discharge standard	✓						
24-hour ambulatory blood pressure monitoring	✓		✓				✓
Immediate blood pressure in the consulting room^b^		✓	✓				
Biochemical function test^c^	✓		✓				
Electrocardiogram	✓		✓				
Scale evaluation^d^	✓		✓	✓		✓	✓
Blinded evaluation			✓				
Adverse reactions/adverse events (ADR/AE)	✓^e^	✓^e^	✓^e^	✓^e^		✓^e^	✓^e^
New drug combinations	✓^e^	✓^e^	✓^e^	✓^e^		✓^e^	✓^e^

^a^“✓” in this table represents the items that must be completed; The participants made corresponding records after treatment.

^b^Immediate blood pressure in the consulting room: it needs to be measured in the first to sixth weeks.

^c^Biochemical function test: liver function, kidney function, blood lipid, etc.

^d^Scale evaluation: Traditional Chinese medicine symptom scale, Dizziness Handicap Inventory (DHI), Headache Impact Test-6 (HIT-6), Pittsburgh Sleep Quality Index (PSQI), 36-Item Short Form Health Survey.

^e^Recorded at any time.

#### Dissemination

At the end of the trial, we will endeavor to share the results with other experts from the Chinese medical field, with the aim of benefiting them by exploring the immediate antihypertensive effects of the “HuoXueSanFeng” acupuncture method and its effects on the central nervous system.

#### Biological Specimens

Routine blood tests will be performed and analyzed to collect the necessary data.

### Ethics Approval

This trial was conducted in strict accordance with the Declaration of Helsinki and relevant Chinese clinical trial research norms and regulations. The study protocol has been approved by the Ethics Committee of the Clinical Research Unit (number: 2024DZMEC-153-03) and was successfully registered on May 23, 2024, at ChiCTR2400084696 (Chinese Clinical Trial Registry). Before each participant is enrolled in this study, the investigator will provide a complete and comprehensive written introduction to the purpose, procedures, and potential risks of the study. Participants will be informed of their right to withdraw from the study at any time. If a participant withdraws during the course of the trial, we reserve the right to retain the data obtained for statistical analysis. All data will be anonymized. All participants are entitled to 18 free acupuncture treatments, as this study does not include compensation for transportation and lost wages.

## Results

This study was registered in China Clinical Trial Registration Center on May 23, 2024. Data collection began in July 2024 and is expected to end in June 2025. At present, the data of this experiment is in the collection stage, 27 participants have been recruited, and the data has not been analyzed. The experimental results are expected to be submitted and published in November 2025.

## Discussion

### Anticipated Findings

This study is a multicenter, randomized, single-blind, sham acupuncture-controlled clinical trial designed to assess the efficacy and safety of the “HuoXueSanFeng” acupuncture method in the management of hypertension.

Hypertension is intricately linked with a range of comorbidities, including cardiovascular disease, chronic kidney disease, and diabetes mellitus [45,46]. The primary focus of hypertension management is the regulation of blood pressure and the protection of target organs. Nonetheless, the global burden, health care costs, and societal impact of hypertension are escalating, particularly in low- and middle-income countries [3,47]. Although oral pharmacotherapy remains the cornerstone of hypertension, many patients experience suboptimal blood pressure control, attributable to factors such as the single-target action of medications and their associated adverse effects [48]. In recent years, nonpharmacological therapies have gained recognition for their efficacy in blood pressure reduction, largely due to their minimal or absent side effects, in both developed and developing nations [49]. As a nonpharmacological intervention, acupuncture offers distinct advantages in the treatment of hypertension, owing to its multitarget, multipathway, and holistic regulatory effects [50,51]. Acupuncture can not only regulate hypertensive conditions caused by the imbalance of sympathetic and parasympathetic nervous systems by activating different brain regions, but also regulate neurotransmitters in related brain regions and alleviate autonomic responses, thus exerting antihypertensive effects [27]. However, there are fewer high-quality clinical studies on the treatment of hypertension with acupuncture, and the following three problems exist. First, there are no detailed studies to assess when acupuncture is effective in lowering blood pressure and its duration. Second, there is a lack of effective integration of symptoms accompanying the disease (eg, headache, vertigo, and insomnia). Consequently, the current scientific basis for the regulation of hypertension by acupuncture is insufficient, and the mechanism of antihypertensive by acupuncture needs to be further elucidation.

The “HuoXueSanFeng” acupuncture method, founded by Academician [name] based on the “Qihai” theory, is used for the treatment of hypertension. In this method, Renying (ST9) is selected as the main point, supplemented by Baihui (BL7), Quchi (LI11), Hegu (LI4), ZuSanli (ST36) and Taichong (LR3), to treat hypertension. In this study, the Renying (ST9) acupoint is selected as the primary focus, with supplementary points including Baihui (BL7), Quchi (LI11), Hegu (LI4), Zusanli (ST36), and Taichong (LR3), to address hypertension. This methodology integrates the specificity of meridian points with anatomical insights from Western medicine. Furthermore, the approach adheres to academic standards for acupuncture techniques and specifies the precise amount of needling required. This acupuncture therapy is regarded as an environmentally friendly, safe, and effective treatment for hypertension. Consequently, the objective of this research was to thoroughly assess both the immediate and short-term antihypertensive effects of “HuoXueSanFeng” acupuncture, employing sham acupuncture as a control group and using office blood pressure and 24-hour ambulatory blood pressure monitoring. In addition, we evaluated the beneficial effects of the acupuncture method using various assessment tools, such as the DHI, HIT-6, and PSQI, to provide robust, evidence-based support for its application in the treatment of essential hypertension.

It is noteworthy that our trial assessed the immediate effect of acupuncture in lowering blood pressure and the persistence of short-term effects, but the long-term efficacy of acupuncture-such as sustained blood pressure control over months or years remains unproven. Hypertension is a chronic disease that requires long-term management, and the durability of nonpharmacologic interventions such as acupuncture must be rigorously evaluated through long-term follow-up studies. Future studies should prioritize longitudinal designs with 6- or 12-month follow-ups to determine whether repeated acupuncture or intensive treatment is necessary to maintain treatment efficacy.

In addition, there are some noteworthy limitations of our trial. The inclusion of patients with essential hypertension was relatively difficult for us because hypertension, if left untreated, increases the risk of cardiovascular and renal complications [12]. To ensure the safety and reliability of the study, we excluded individuals with severe complications in strict accordance with the inclusion criteria. However, as a double-blind design could not be realized in this experiment, we used sham acupuncture as a control and tried to maintain the consistency of the operation between the 2 groups as much as possible. At the same time, we assessed the effectiveness of blinding in time to achieve a single-blind design. Blinding could not be applied to the acupuncturists because they could perceive the sensation under the needle and visually recognize the needling device during the procedure.

